#### Female Sexual Function Index (FSFI)

It has been designed by Rosen et al. to evaluate sexual function in women over the past 4 weeks [31]. It consists of 19 items subdivided into six subcategories of sex desire (2 items), arousal (4 items), lubrication (4 items), orgasm (3 items), satisfaction (3 items), and pain (3 items). These subcategories have response ranges from 0 or 1 to 5, with higher scores indicating better sexual performance [32]. The questionnaire has been used in many studies abroad and has shown to have a high degree of internal consistency, reliability, and validity [33]. The findings of Fakhri and Mohammadi’s study showed that the Farsi version of FSFI, FSFI-IV, is a reliable and valid instrument with appropriate psychometric properties to evaluate women’s sexual function [32, 34]. Reliability of the scale has been calculated through stability analysis or calculation of the internal consistency coefficient. The Cronbach’s alpha coefficient was 0.70 and was higher for all domains and for the whole scale [34]. In addition, reliability was confirmed by the test-retest method and the correlation coefficient was reported high indicating that FSFI-IV is reusable within a 4-week interval [31, 35–38]. The maximum score for each domain is 6 and for the whole scale is 36. Also, any score less than 28 will be used to indicate sexual dysfunction [34].

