### Primary outcome

Primary outcome of this study is to investigate changes of sexual function using the FSFI.

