### Study procedure

After obtaining the necessary permissions from the Ethics Committee of Qazvin University of Medical Sciences, registration at the Iranian Clinical Trial Registration Center (IRCT), and obtaining the permission from Qazvin Nursing and Midwifery School, the researcher will attend for recruitment in Qazvin Health Centers. The lactating women of each center will be invited for participation. The process and purpose of the research will be explained to those who meet the inclusion criteria. Also, they will be ensured that their information will be kept confidential and that the questionnaires will be anonymous and coded in accordance with the research ethics. They will enter into the study after signing the written consent form. The researcher will ensure that they can leave the study at any time. After enrolling eligible individuals, a simple block randomization will be used. Participants will be randomly assigned to the intervention and control groups.

The questionnaires will be filled out by the participants before the intervention. Then, the intervention (acupressure) will be performed as mentioned above. Evaluation of sexual function in both the intervention and control groups will be performed using the FSFI questionnaire immediately, 1 and 2 months after the intervention. Figure 3 provides the timeline of recruitment, allocation, and assessment.

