### Statistical analysis

Data will be analyzed using the chi-square test, Fisher exact test, and independent *t* test via the SPSS v.24 software. The Kolmogorov-Smirnov and Shapiro tests will also be used to check for the normal distribution of sexual function scores. Descriptive statistics (number, mean, and standard deviation) will be used to describe the demographic characteristics of the participants. The repeated measure ANOVA will be used to compare the mean sexual function of women before and after the intervention. The significance level of all tests is set as *p* < 0.05.

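### The primary FSFI claim is tied to no score, visit or between-arm test, so it could rest on a before-after change or on whichever visit is significant

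*Protocol article*

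**What the plan says.** - **Primary outcome.** The section is one sentence: "Primary outcome of this study is to investigate changes of sexual function using the FSFI". It gives no score, time point or effect measure.
- **Visits.** The Study procedure section has both groups assessed "using the FSFI questionnaire immediately, 1 and 2 months after the intervention", in addition to baseline. The Abstract gives the same schedule. Neither ranks the three visits.
- **Scores.** The FSFI section describes six domains and a total: "The maximum score for each domain is 6 and for the whole scale is 36". It adds a cut-off for dysfunction at 28. Only the Sample size calculation points to one of these, because it uses means and standard deviations of the total score.
- **Analysis.** The Statistical analysis section states: "The repeated measure ANOVA will be used to compare the mean sexual function of women before and after the intervention". Chi-square, Fisher exact and independent t tests are listed beside the ANOVA with no purpose assigned. The section ends: "The significance level of all tests is set as" p < 0.05. No order of tests is given.

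**The concern.** A repeated-measures ANOVA with two arms yields a group effect, a time effect and a group-by-time interaction. Only the first and third compare the arms. The protocol's description, means before and after the intervention, fits the time effect best.

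That matters in this population. The Background says that the sexual problems of lactation usually resolve within a year of childbirth, and the Participants section enrols women 6 to 12 months after it. Ten sessions at 4-day intervals take about 40 days, and the last assessment is 2 months later, so follow-up runs roughly 100 days from baseline. For women enrolled early, this falls inside the period of expected recovery. A significant before-after change could appear in both arms with no effect of the seeds.

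Separately, with three unranked visits, the authors could report the one visit where the arms differ as the primary result. In either case a reader could not tell whether the primary claim had been fixed in advance.

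**Working it through.** **1. What the trial was sized for.** Inputs from the Sample size calculation: total-score means 24.65 and 22.27 (difference 2.38), SDs 3.47 and 3.03, α = 0.05, power 80%, 10% loss. Assumed: a two-sided test, and the larger SD in both arms.

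n = 2 × (1.960 + 0.842)² × 3.47² / 2.38² = 2 × 7.85 × 12.04 / 5.66 ≈ 33.4, so 34 completers. Then 34 / 0.9 = 37.8, so 38 per group, as stated. The plan's figure is thus reproduced by one comparison of the total score at 5%. (The stated error d = 5 plays no part in this.)

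**2. If any of the three visits could count.** With no true effect and independent visits, the chance of at least one p < 0.05 is 1 − 0.95³ = 14.3%. Repeated scores on the same women are correlated. The documents give no correlation, so a range is assumed. Simulation: 40,000 trials, 34 completers per arm, a two-sample t test at each visit.

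| Assumed correlation between visits | At least one p < 0.05 | At least one favouring acupressure |
|---|---|---|
| 0.3 | 13.5% | 6.6% |
| 0.5 | 12.6% | 6.3% |
| 0.7 | 11.0% | 5.4% |
| 0.9 | 8.2% | 4.2% |

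The nominal rates are 5% and 2.5%.

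**3. If the time effect could count.** The documents do not give the size of natural recovery. As an illustration, let both arms improve equally by half the planning difference, 1.19 points, with SD 3.47. The standard error of the mean change from baseline to one later visit, over 68 completers, is 3.47 × √(2(1 − ρ)/68):

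- ρ = 0.3: 0.498, so z = 1.19/0.498 = 2.4
- ρ = 0.5: 0.421, so z = 2.8
- ρ = 0.7: 0.326, so z = 3.7

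All exceed 1.96, although the arms do not differ at all.

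**4. What a single named test would do.** Assume a difference of 2.38 at every post-intervention visit, SD 3.47, and equal correlation ρ among all four assessments. The residual variance of the three-visit mean after baseline adjustment is 3.47² × [(1 + 2ρ)/3 − ρ²].

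- ρ = 0.3: 12.04 × 0.443 = 5.34, SD 2.31; SE = 2.31 × √(2/34) = 0.560; z = 2.38/0.560 = 4.2
- ρ = 0.7: 12.04 × 0.310 = 3.73, SD 1.93; SE = 0.469; z = 5.1

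Power is at least about 98% in both cases. Simulation under the same assumptions gave about 98 to 99% for this contrast, 66 to 85% for the ANOVA group effect and 68 to 97% for group-by-time. All three held type I error at about 5%.

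**5. The alternative of keeping any of three visits with Bonferroni.** At 0.05/3 = 0.0167 (z = 2.394), power at a given visit with 34 completers is Φ(2.38/(3.47 × √(2/34)) − 2.394) = Φ(2.83 − 2.39), about 67%. Restoring 80% needs 2 × (2.394 + 0.842)² × 12.04/5.66 ≈ 44.5, so 45 completers, or 50 per arm with 10% loss.

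**The case against.** **The named model already spans the visits.** The Abstract names repeated-measures ANOVA at 0.05 and no other test. A single group or group-by-time test on the total score would hold 5% over all visits. That is correct, and it means that the rates in step 2 are conditional. But the protocol does not say that either effect decides, and its before-after wording points elsewhere.

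**A reader might infer that any one significant comparison counts as success.** No section says so. A threshold for each test is not a definition of trial success. Nor are t tests assigned to FSFI at each visit; baseline comparisons, or SQOL-F with its one follow-up, would explain their listing equally well.

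**A reader might also multiply the tests by the six domains and reach a far higher error rate.** The documents do not support this. The domains appear only where the instrument is described, no section makes one an outcome, and the sample size rests on the total.

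**Detail may sit in an analysis plan that is not shown.** For the purpose of the t tests or the handling of secondary comparisons, that is fair, and their absence is not criticised here. The score and time that define the primary outcome are protocol content, however, and the article has a section for them that leaves both open. The before-after description is a statement made, not a detail omitted.

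**Conclusion.** The point holds as a gap in the definition of the primary outcome. The total score is implied by the sample size but not stated. The primary visit and the deciding between-arm effect are neither stated nor implied. The plan does not prevent a primary claim based on a time effect common to both arms, or on a visit picked after the results are seen.

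If visit-wise picking on the total score were allowed, the two-sided false-positive rate would be about 8% to 13.5%. This rests on assumed correlations of 0.9 to 0.3, normal scores and 34 completers per arm; about half of those errors would favour acupressure. The documents do not support saying that the trial's actual error rate is above 5%. A single pre-specified group or group-by-time test would keep it there. The time-effect illustration depends on an assumed amount of recovery, but it needs only a modest one.

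This should be settled before unblinding. It does not invalidate the design.

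**What to change.** Replace the primary outcome sentence, and align the Statistical analysis section, with wording such as:

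*The primary endpoint is the FSFI total score. The single primary test is the baseline-adjusted difference between arms, averaged over the three post-intervention assessments, at two-sided 0.05. Differences at individual visits and SQOL-F at 2 months are secondary. Domain scores are descriptive. Changes over time within or across arms are descriptive and do not support a claim of efficacy.*

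One visit, named before unblinding, is an acceptable alternative to the average. Naming the group-by-time test on the total score would also close the gap within the existing model, but with less power under the assumptions in step 4.

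The cost is wording and a matching registry update. The data are already scheduled, and 38 per group still fits a single test at 0.05. The trial gives up the freedom to call other significant results primary.

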### Methods to protect against bias

#### Randomization and allocation

Sampling will be made using a two-step sampling method. In the first step, Qazvin City will be considered as five geographical districts. Next, two health centers will be randomly selected in each of these five districts of Qazvin City. Secondly, women referred to selected health centers will be assessed for eligibility and, in case of willingness to participate in the study, will be recruited. They will be randomly assigned to two groups as follows: One letter is assigned to each group (A: intervention group, B: control group), and all possible conditions for the 4-block will be written and numbered, as follows: 1.AABB 2.ABAB 3.BBAA 4.BABA 5.ABBA 6.BAAB 7.

In a simple block randomization method (using the table of random numbers), numbers of blocks will be selected until the specified sample size is achieved. The random allocation sequence is specified. For example, if the numbers given are 3, 2, 2, 1, and ..., respectively, the allocation sequence will be as follows: AABB ABAB ABAB BBAA. As a result, each participant will have a unique code (*n* = 76).

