### Role and qualification of practitioners

The research team consists of one specialist in auriculotherapy (TO), two specialists in reproductive health (ZA and NB), and one midwifery postgraduate student. The protocol of intervention was designed based on the literature review and expert opinion of TO who is an expert in auriculotherapy and is a journal editor for several international journals. Other team members have been qualified in this technique before designing present research. Participant screening and care providing will be done by SB, and ZA and NB will monitor her during the first 10 sessions to ensure the fidelity of providing intervention.

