### Sample size calculation

Sample size is estimated according to the study of Bokaie et al. with the mean and standard deviation of total sexual function score has been reported as 24.65 ± 3.47 and 22.27 ± 3.03 in the intervention (telephone counseling group) and control groups, respectively [30]. Therefore, considering the first type error (α) = 0.05 (95% confidence), the second type error (β) = 0.2 (80% power) and error *d* = 5, and the possibility of 10% loss to follow-up, 38 individuals for each group are required. So, the total sample size will be 76 people.

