#### Treatment fidelity

One of the researchers (SB) is responsible to perform intervention. She has participated specific course on auriculotherapy and is supervised by acupuncturist (MHA) about how to perform the intervention. Approximately 15% of intervention sessions will be run under supervision of the acupuncturist to ensure that all acupoints are chosen correctly.

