#### Ethical and safety issues

The research protocol will be reviewed and approved by the Ethics and Human Research Committee of Qazvin University of Medical Sciences (decree code: IR.QUMS.REC.1398.056). It is registered on the Iranian Clinical Trial Registration Center under decree code of IRCT20190626044028N1. In addition, the following ethical considerations will be considered throughout this research: obtaining written informed consent, the volunteer nature of participation in the study, ability to withdraw from the study at any time, and confidentiality of information even during the publication of findings. All ethical issues related to clinical trials will be considered. Informed consent during recruitment phase will be obtained by SB.

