## Discussion

To the best of our knowledge, this study is the first randomized clinical trial investigating the effect of ear acupressure on the sexual function of lactating women. The strength of this study is the randomized design with parallel treatment procedures and a large sample size, but due to the importance of the treatment practitioner knowing whether they are placing an adhesive patch with a *Vaccaria* seed or without one, a true double blind study is not possible. Acupressure has no known side effects, is non-invasive, and is easy to use [20, 21]. Therefore, the therapist and clients can develop a sense of closeness, trust, and confidence [20]. Several studies have shown promising results about the effect of ear acupressure on insomnia [20, 22], menstrual cramps and dysmenorrhea [21, 23, 24], premenstrual pain [25], chemotherapy-induced nausea and vomiting [26], smoking cessation [27], obesity [18], and shortness of breath [28]. In the study of Oakley et al., acupuncture was affective in premenopausal women with sexual function [43]. In line with previous literature, this study would provide insights about the impact of ear acupressure on sexual function in lactating women.

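### Fixed, disclosed blocks of four, with one unblinded researcher recruiting and treating, would let someone who keeps count determine on average a third of allocations if women are randomised one by one

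*Protocol article*

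**What the plan says.** All references are to the protocol article; no separate analysis plan is at hand.

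- **Sequence.** Under Randomization and allocation, "all possible conditions for the 4-block will be written and numbered". The six balanced arrangements of two A and two B are listed, and "numbers of blocks will be selected until the specified sample size is achieved". Neither a second block length nor stratification by health centre is described.
- **Size.** Sample size calculation: "38 individuals for each group are required. So, the total sample size will be 76 people". That is 76 / 4 = 19 complete blocks.
- **Roles.** Under Role and qualification of practitioners, "Participant screening and care providing will be done by" a single researcher. Under Ethical and safety issues, "Informed consent during recruitment phase will be obtained by" the same person. Under Treatment fidelity, that person "is responsible to perform intervention".
- **Blinding.** The Discussion concedes that a true double-blind study is not possible, "due to the importance of the treatment practitioner knowing whether they are placing an adhesive patch" with a seed or without. The Blinding section names participants, outcome assessor and analyst as blind. It does not name the practitioner or recruiter.
- **Concealment.** Someone outside the team prepares the sequence and places it in opaque, sealed, consecutively numbered envelopes.
- **Worked example.** For draws 3, 2, 2, 1, "the allocation sequence will be as follows: AABB ABAB ABAB BBAA".

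**The concern.** Allocation concealment is meant to ensure that whoever decides to enrol the next woman cannot foresee her arm. Here that person also sees past allocations as she places the patches, and the block rule is printed in her own protocol. With a constant block of four, two like allocations at the start of a block settle the other two, and the fourth is always settled by the first three. An envelope does nothing against that deduction.

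Entry leaves some room for judgement: willingness to take part and ability to attend every session are inclusion criteria. A recruiter who expects a given arm next could, without intending it, vary whom she approaches or how firmly. Blinding after randomisation cannot repair groups that differed on entry.

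The worked example also does not follow from the numbered list that it illustrates.

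**Working it through.** **1. Number of blocks.** The plan gives no predictability figure; its own relevant figure is the sample size. With difference 24.65 − 22.27 = 2.38, SD 3.47 in both arms, alpha 0.05 (two-sided assumed) and 80% power:

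n = 2 × (1.960 + 0.842)² × 3.47² / 2.38² = 33.4, so 34; 34 / 0.9 = 37.8, so 38 per group.

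This reproduces 38 and 76, hence 19 blocks of four.

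**2. Determinable allocations.** An allocation is determinable once one arm's quota of two in the block is full.

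| Block | Determinable positions |
|---|---|
| AABB, BBAA | 3 and 4 |
| ABAB, BABA, ABBA, BAAB | 4 only |

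Total: 2 × 2 + 4 × 1 = 8 of 24 positions, or one third. By position the chances are 0, 0, 1/3 and 1. Over 76 women: 76 / 3 = 25.3 expected (SD √(19 × 1/3 × 2/3) = 2.1). The minimum is 19, the last of every block; the maximum is 38.

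**3. Best-guess accuracy.** Position 1: 1/2. Position 2: 2/3. Position 3: (1/3) × 1 + (2/3) × 1/2 = 2/3. Position 4: 1. The mean is (0.5 + 0.667 + 0.667 + 1) / 4 = 0.708.

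**4. What that could do to the result.** Suppose the recruiter enrols women whose expected outcome is higher by η when she guesses one arm and lower by η when she guesses the other. With a proportion p of guesses correct, the arm difference shifts by 2η(2p − 1) = 2η × 0.4167 = 0.83η. The documents give no value for η, so a range is shown:

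| η (FSFI points, assumed) | Shift in arm difference |
|---|---|
| 0.25 | 0.21 |
| 0.5 | 0.42 |
| 1 | 0.83 |

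This assumes that she acts on every guess, including uncertain ones, and that the whole shift reaches the estimate.

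**5. Alternatives.**

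- One random permutation of 38 A and 38 B. Accuracy = [38 + (2^76 / C(76,38) − 1) / 2] / 76 = [38 + (10.96 − 1) / 2] / 76 = 0.565. Expected determinable allocations = 2 × 38 / 39 = 1.9. Applied to a block of four, the same formulas return 0.708 and 4/3, agreeing with steps 2 and 3. Shift: 2η × 0.13 = 0.26η.
- Undisclosed mixed blocks, by simulation with an observer who knows the possible lengths but not their order. Lengths 4/6 leave about 5.5% of allocations determinable (about 4 of 76) and about 69% of guesses correct. Lengths 4/6/8 leave about 68% correct, a shift of 2η × (2 × 0.678 − 1) = 0.71η.
- Larger fixed blocks: 25% determinable for blocks of six and 20% for blocks of eight.

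**6. Worked example.** In the printed list, 1 = AABB, 2 = ABAB and 3 = BBAA. Draws 3, 2, 2, 1 therefore give BBAA ABAB ABAB AABB. The printed sequence corresponds to 1, 2, 2, 3.

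**The case against.** The best reply is that the one-third figure is conditional. The article does not say who opens the envelopes or when. Study procedure places randomisation after enrolment without saying whether this is woman by woman or in batches, and recruitment runs over ten centres. If several women were enrolled before any envelope was opened, fewer allocations could be foreseen. This stands. Consecutively numbered envelopes fit one-by-one use but do not prove it. A reader might infer that a third of allocations will in fact be known, or that the envelopes conceal nothing. The documents support neither: someone must keep count, and two thirds of allocations are on average not certain even then.

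A reader might also set the 0.83-point shift against the planned 2.38 (0.83 / 2.38 = 35%) and call that the bias. The 1-point shift behind it is purely an assumption. FSFI is also measured before treatment, the primary outcome is its change, and the repeated measures analysis compares scores before and after. A stable difference in starting level would partly cancel; selection on expected improvement would not.

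The protections are real: a sham control, blinded participants, assessor and analyst, a participant-completed FSFI, and an outside person preparing the sequence. They limit bias after entry and protect the stored sequence. None prevents deduction from past allocations by the person recruiting.

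Finally, the reversed example might be read as making the sequence impossible to audit. It does not: the numbered list defines the rule, and every block in the example is valid.

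**Conclusion.** The point holds as a conditional weakness in concealment. A constant, disclosed block of four is combined with one unblinded person who screens, consents and treats. Given one-by-one randomisation and a researcher who keeps count, on average 25 of 76 allocations (19 at the least) are determinable before the next enrolment, and 71% can be guessed correctly against 50% with no predictability. Selection at entry is possible; nothing in the documents shows that it will occur or that anyone intends it. The size of any bias is unknown. It scales as 0.83 times an assumed shift, before any cancellation through the baseline comparison. The point challenges what the article fixes, not detail left to a fuller document, and it merits action mainly because the remedy is so cheap. The worked example is an editorial slip with no effect on these figures.

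**What to change.** 1. Have the outside person already responsible for the sequence generate one random permutation of 38 A and 38 B in place of the blocks of four. Best-guess accuracy falls from about 71% to about 56.5%, and determinable allocations from about 25 to about 2.
2. Withhold the details of the scheme from the researcher who recruits. The block length is already printed in the article, so a new scheme is safer than trying to hide the present one.
3. If blocks are kept, use randomly mixed lengths unknown to the team. This is the weaker choice: it removes most certain calls but leaves guessing near 68%. Keeping enrolment decisions apart from knowledge of past allocations would then matter more.
4. Correct the example for draws 3, 2, 2, 1 to BBAA ABAB ABAB AABB, or delete it.

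Items 1, 2 and 4 need no extra staff or patients. The cost of a single permutation is a possible slight imbalance between arms if recruitment stops before 76. No stratification by centre is described, so none is lost.
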